## Abstract

**Introduction:**

Medication use in pregnancy is common and increasing. Pregnant women are often excluded from drug trials, therefore the safety to mother and baby of many medications used in pregnancy is unknown. Routine health data have been used to look for evidence of harm and safety of specific medications, but not to systematically look across all prescribed medications in pregnancy.

**Aims:**

To systematically identify medications prescribed during pregnancy requiring further research into their potential harms to mother or baby.

**Methods:**

We will describe trends in primary care prescribing in pregnancy over time, and socio-demographic patterning of prescribing, using data from pregnancies in the Clinical Practice Research Datalink (CPRD). We will identify and categorise maternal, fetal, and infant adverse outcomes reported in the CPRD and linked hospital and mortality data. We will use Bayesian signal detection models to analyse all medication/outcome pairs to identify where an outcome occurs significantly more frequently in mothers prescribed a specific medication than in mothers not prescribed it. Potential confounders will not be accounted for at this stage. Published evidence on the identified medication/outcome pairs will be reviewed and incorporated with the results from trends and signal detection analyses. These data will be used by Patient Involvement and Study Advisory Board workshops to prioritise medications for further research, with medications more commonly prescribed for underserved groups being given precedence. For three prioritised signals, cohort analyses will compare the occurrence of adverse outcomes in those prescribed compared to those not prescribed the medication of interest, adjusting for maternal morbidity, co-medications, and other measured confounders.

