### Exposures

Data on all primary care prescriptions from 90 days prior to pregnancy through to the end of pregnancy, including those that have been initiated in secondary care and continued in primary care, will be extracted. Prescribing patterns will be assessed throughout pregnancy and by trimester and 90 days prior to pregnancy start. Trimesters will be defined as per the CPRD pregnancy register. Medications will be classified using British National Formulary (BNF) and Anatomical Therapeutic Chemical (ATC) systems.

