**Availability of alternative medications with known safety**

The potential for change in prescribing practice is greater for medications where there are alternative medications that can be prescribed for any given indication. In cases where there are not known safe alternatives the risks of not taking a given medication will be an important consideration.

Initial collation of information gathered from the above 5 domains will be done by the study team and formatted in an appropriate way for an initial PPI workshop. Output from this workshop will be added to the information from the initial 5 domains and taken to the Study Advisory Board Workshop. The multidisciplinary team will review information from the 5 domains and PPI discussions prior to the workshop and during the workshop will have small group and whole group discussions through which a prioritised list of medications will be generated.

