### Objective 4: Retrospective cohort studies for identified signals

Retrospective cohort studies of three prioritised medication signals will be done, to quantify associations with adverse outcomes while adjusting for confounding. Details of the analysis plan will be determined by the specific drug and outcome being investigated.

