### Limitations

As an observational study based on routinely collected data, there is potential for misclassification of exposures, outcomes, and of pregnancy status. The CPRD pregnancy register is based on an algorithm that searches for clinical codes likely to indicate pregnancy and generates estimated gestational dates from this. Some of the clinical codes used may generate false pregnancies, as has been highlighted in analyses of valproate use where the use of codes such as ‘*Advice on risk harm to fetus from maternl medictn dur preg’* are used when a patient is not pregnant [28]. To minimise the impact of this, where a pregnancy is based on a single code, the appropriateness of including these pregnancies will be reviewed based on the original codes used. Where HES linkage is available, we will also use this to triangulate whether a pregnancy is a true pregnancy, pregnancy outcome, and estimated gestation dates [17].

There is also the potential for residual confounding, particularly confounding by indication, which may not be possible to fully address through statistical adjustment. Prescription records indicate medications issued in primary care but we do not have data on whether prescriptions were collected and taken, so exposure misclassification must be considered.

Outcome misclassification is also possible due to imperfect coding, variation in recording practices, and limited clinical detail for some outcomes. Although signal detection methods are designed for hypothesis generation rather than causal inference, there remains a risk of identifying spurious associations arising from multiple testing or correlated exposures and outcomes. For these reasons, signals identified in this study will be interpreted cautiously and used primarily to prioritise medications for further investigation rather than to draw any definitive conclusions about causality.

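### The only comparator named for the three cohort studies is women not prescribed the medicine, and nothing in the design addresses the confounding by indication that the article says adjustment may leave behind

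*Protocol article*

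**What the plan says.** The Methods paragraph of the abstract describes the cohort stage: "cohort analyses will compare the occurrence of adverse outcomes in those prescribed compared to those not prescribed the medication of interest". This is the only place where a comparator for these studies is named. The same sentence gives the means of control as "adjusting for maternal morbidity, co-medications, and other measured confounders". The Objective 4 section repeats the aim of quantifying associations while adjusting for confounding, names no comparator, and adds: "Details of the analysis plan will be determined by the specific drug and outcome being investigated".

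Under Limitations the article says: "There is also the potential for residual confounding, particularly confounding by indication, which may not be possible to fully address through statistical adjustment".

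Three other sections describe material that could supply a comparator closer to the users:

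- Exposures: the extract covers "Data on all primary care prescriptions from 90 days prior to pregnancy through to the end of pregnancy".
- Covariates: comorbidities at the start of pregnancy are taken from primary care and hospital codes.
- Objective 3, on availability of alternatives: prioritisation considers whether "there are alternative medications that can be prescribed for any given indication".

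Under Dissemination, an adverse outcome found to be associated with any of the three medicines will be presented to the regulator.

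**The concern.** Women prescribed a medicine differ from women not prescribed it first of all in having the condition it treats. Adjustment for recorded morbidity removes part of that difference. What the records capture poorly, such as severity, can remain. The article names one tool, adjustment for measured confounders, says that this tool may not be enough, and states no design feature to back it up.

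Two features make this weigh more here than in an ordinary cohort study. First, the signals are generated by comparing prescribed with not-prescribed mothers without accounting for confounders, so signals caused by the indication should be expected among the candidates. Testing them with the same contrast plus measured covariates is a weak check on that explanation. Second, the route to the regulator opens on an association being found, and no comparison with women who share the indication is planned to help interpret it.

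**Working it through.** **Reading the passages together.** The abstract states the contrast. The Objective 4 section defers details and neither withdraws nor qualifies the contrast. The Limitations section says adjustment may fall short. In Objective 3, pairs are annotated for known indication effects and the likelihood of confounding by indication is discussed with clinicians. Those steps influence which medicines are chosen; they do not change the comparator used afterwards. The Exposures, Covariates and Objective 3 sections show that the means for a closer comparator are already in hand.

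**Figure to reproduce.** None. The article gives no sample size, event rate, effect size or power for the cohort studies, so the size of the bias cannot be computed from it.

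**Illustration; every input is assumed.** Take a medicine with no effect and a binary factor (the part of indication or severity left after adjustment) that multiplies the outcome risk by R. Let p1 be its prevalence in the prescribed group and p0 its prevalence in the comparator. The spurious risk ratio is

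bias = [1 + p1(R − 1)] / [1 + p0(R − 1)].

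With p1 = 0.60:

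| R | General not-prescribed group, p0 = 0.05 | p0 = 0.20 | Comparator sharing the indication, p0 = 0.40 | p0 = 0.50 |
|---|---|---|---|---|
| 1.5 | 1.30/1.025 = 1.27 | 1.30/1.10 = 1.18 | 1.30/1.20 = 1.08 | 1.30/1.25 = 1.04 |
| 2 | 1.60/1.05 = 1.52 | 1.60/1.20 = 1.33 | 1.60/1.40 = 1.14 | 1.60/1.50 = 1.07 |
| 3 | 2.20/1.10 = 2.00 | 2.20/1.40 = 1.57 | 2.20/1.80 = 1.22 | 2.20/2.00 = 1.10 |

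Extreme case, with the factor present in every user (p1 = 1) and in 2% or 10% of the comparator:

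- R = 1.5: 1.5/1.01 = 1.49; 1.5/1.05 = 1.43
- R = 2: 2/1.02 = 1.96; 2/1.10 = 1.82
- R = 3: 3/1.04 = 2.88; 3/1.20 = 2.50

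The extreme case is an upper bound. A factor universal in users and rare in others looks much like the indication itself, which adjustment for recorded morbidity is meant to capture. What carries over from the illustration is the direction: the bias shrinks as p0 approaches p1, and that is what a comparator sharing the indication is meant to achieve.

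**The case against.** The strongest reply is that nothing is settled yet. The contrast stands in one sentence of the abstract, the operative section defers to drug-specific plans, and the medicines will not be chosen until prioritisation ends in spring 2027. The right comparator depends on the drug. A woman who stopped before pregnancy, or who takes an alternative, is also a woman not prescribed the medicine during pregnancy, so the stated wording does not exclude either group. The article also adjusts for morbidity and co-medications, screens for indication effects before selection, and discloses residual confounding.

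Most of this is right, and it limits the point. A reader might infer that the three studies are locked into users against all non-users. The documents do not support that: the contrast is stated, not fixed, and the word all is not there. A reader might also infer that the studies cannot meet Objective 4. That does not follow either, because the objective is to quantify associations after adjustment, not to isolate causation.

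What the reply does not answer is that the deferral commits the later plans to nothing on indication. Those plans will be written once the signals are known, when the choice of comparator could be influenced by results. A minimum set now avoids that.

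**Conclusion.** The point holds as a worthwhile improvement to a stated method, not as an error or a contradiction. The article names one comparator, concedes that its one means of control may leave confounding by indication in place, and describes data that would support a closer comparator without committing to use them.

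The size is unknown. The illustration gives a spurious risk ratio of about 1.2 to 2.0 for a medicine with no effect, and up to 2.9 in the extreme case, against 1.04 to 1.22 with a comparator sharing the indication. These figures rest entirely on the assumed prevalences and risk ratios and on a single binary factor left after adjustment. The real bias depends on the medicines chosen and could be small where the indication has little bearing on the outcome.

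**What to change.** Keep the prescribed versus not-prescribed contrast. Add to the Objective 4 section that each cohort study will also report, where the data allow, at least one comparator sharing the indication:

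- women prescribed the medicine in the 90 days before pregnancy but not during it;
- women prescribed an alternative for the same indication; or
- non-users restricted to the recorded indication.

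Each drug-specific plan should name its comparator, with the reason, before outcomes are analysed against it. Report all contrasts side by side, including to the regulator, and interpret the non-user estimate in their light. Submission should not be conditional on agreement between them: the added groups are smaller and less precise, and such a condition could hold back a real safety association.

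The cost is some further analysis of data already extracted, smaller comparator groups and wider intervals. Each option has limits. Women who stopped may have milder disease, were exposed in a window that Objective 2 itself analyses, and are of little use for medicines started in pregnancy. An alternative may not exist, or may share the harm and so mask it. Restriction to the recorded indication still leaves unrecorded severity.

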**Discussion:**

This project will provide a list of medications used in pregnancy that should be prioritised for further safety research. Results of three detailed retrospective cohort studies will contribute to informed decision making for patients and clinicians. Study grant number: NIHR207172; CPRD accepted protocol number: 24_004518.

## Introduction

Medication use in pregnancy is common and increasing [1–4]. However, randomised controlled trial evidence on medication safety (to mother and baby) is lacking because pregnant women are often excluded from clinical trials [5]. Using routine databases is one way that we can begin to fill the research gap that is left from the exclusion of pregnant women from drug trials [6,7]. Safety of medications in pregnancy emerged as a top priority of both the public and stakeholders (clinicians, researchers, charities) in a recent review of pregnancy research [8], and in the 2023 UK Women’s health strategy [5].

Changing socio-demographic and health profiles mean that UK women are now having pregnancies at older ages with more comorbidities, and are therefore more likely to take medications during pregnancy [9]. Some studies estimate that over 80% of women in high income countries take a prescribed medicine during their pregnancy [1,2,9,10]. There are also important changes in prescribing practices. Anti-depressant use in women of childbearing age has been increasing year on year in the UK, from 2.1 million women aged 15–49 in 2016 to 2.6 million in 2024 [11]; this has implications for the number of women exposed in pregnancy and requires further investigation [11–13]. Understanding the variations in medication use in pregnancy over time, and between different socio-demographic groups, can highlight important factors that could contribute to bias and confounding. It is therefore important that descriptive analyses of trends precede subsequent drug safety studies.

There is a growing number of medications that would benefit from greater information on safety of use in pregnancy. Once a concern has been raised about a medication that is being prescribed in pregnancy being potentially harmful, studies can be undertaken to evaluate the harm. However, to our knowledge, there are no studies that are aimed at systematically identifying potential maternal, fetal, and infant harms of medications in pregnancy, which could then be prioritised for further research into their safety. This is important when so many of the medications used in pregnancy have insufficient safety data. Signal detection is the process of looking at pattens of adverse outcomes within datasets to identify potentially causal associations between a medication and the adverse outcome. Statistical methods are available that allow for analysing a large number of medications and outcomes at once, identifying a small number of medications where an outcome is occurring more often than would be expected from chance alone. These approaches are well established in general pharmacovigilance but have rarely been applied to the full range of maternal, fetal, and infant outcomes in pregnancy. Applying such methods to linked primary care, hospital, and mortality records provides an opportunity to identify previously unrecognised safety signals. This in turn enables us to prioritise medications that need further research into their safety.

This project will investigate safety of medications by evaluating a wide range of potential adverse outcomes for mother, fetus and infant based on the set of core data elements for pregnancy pharmacovigilance developed by the European Network of Teratology Information Services and including maternal and infant mortality, maternal medical conditions arising in pregnancy, delivery and post-partum complications, fetal loss and neonatal and infant morbidity [14].

## Materials and methods

The overarching aim of this study is to identify medications that may be harmful to the mother, fetus, or infant, when prescribed during pregnancy.

The specific objectives are:

To describe temporal trends in medications prescribed during pregnancy in primary care in England over the past 20 years, and to examine variation by maternal age, ethnicity, socio-economic status, geographical region, and comorbidities.To apply Bayesian signal detection methods to identify medications potentially associated with adverse maternal, fetal, or infant outcomes.To integrate signal detection results with existing scientific evidence and expert and patient input in order to prioritise medications requiring further investigation.To conduct detailed retrospective cohort studies of three prioritised medications to quantify associations with adverse outcomes after adjusting for confounding.

### Data source

This is a population-based observational study using routinely collected electronic health records from the Clinical Practice Research Datalink (CPRD) Gold and Aurum databases. Pregnancy episodes will be identified using the CPRD Pregnancy Register, with linkage to Hospital Episode Statistics (HES), Office for National Statistics (ONS) mortality records, Index of Multiple Deprivation (IMD) data, and the Mother–Baby linkage for ascertainment of infant outcomes (Fig 1).

**Fig 1 pone.0349045.g001:**
[figure not shown]
Study population and data sources for exposures and outcomes.

We will use data from the CPRD pregnancy register to identify pregnancy episodes and estimated delivery dates and the Mother-Baby link to identify infant outcomes [15,16]. CPRD contains data contributed by GP practices using Vision (Gold) and EMIS (Aurum) clinical systems. The CPRD pregnancy register has been validated against linked HES and the ONS live birth data [15]. Data will be linked to HES data, ONS death registration data, and IMD data.

The study protocol was approved by CPRD’s Research Data Governance group (Ref: 24_004518). Based on these approvals individual patient consent was not required.

Analyses will be conducted within CPRD Safe (trusted research environment).

### Study population

The study will include women in the CPRD pregnancy register who have been registered for at least six months before the start of each pregnancy to ensure sufficient recording of long-term health conditions. An individual woman can contribute more than one pregnancy. The CPRD pregnancy register uses an algorithm based on primary care records to generate information on likely pregnancies, dates, and outcomes. This pregnancy register has been validated and can be supplemented with hospital admissions data to further improve accuracy of information on pregnancy dates and outcomes [15,17,18].

Non-singleton pregnancies will be excluded. Mother and baby will be followed up for up to one year after birth to look at maternal post-partum and infant outcomes.

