## Statistical analysis

### Objective 1: Descriptive analysis

Individual medications will be grouped into summary categories broadly based on BNF chapter and section (S1 Table) [23]. Binary variables will be created for whether a medication from each of the categories was prescribed at any time during the pregnancy, each trimester of pregnancy individually, and for the three-month period prior to the start of pregnancy. Rates of prescribing of each medication category will be calculated per 1000 pregnancies.

To look at trends over time, rates of prescribing will be calculated for each year separately, with a pregnancy assigned to a single year based on the start date of the pregnancy.

Factors influencing the prevalence of prescribing of medication groups during pregnancy will be investigated by modelling whether a prescription was issued for a given medication group during pregnancy, using multivariable logistic regression models including variables such as maternal age, ethnicity, geographical region, deprivation, and comorbidities.

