### Objective 2: Signal detection

Adverse outcomes will be defined as above. Exposures will be prescriptions of individual active ingredients of medications. The estimated dates of pregnancy will be used to identify any medications prescribed in the three months prior to pregnancy or during pregnancy, and analyses will be run for each trimester separately as well as for the three-month period prior to pregnancy.

We will apply standard Bayesian signal detection models using the Information Component (IC) [24–26]. This method is based on comparing the frequency of occurrence of the outcome of interest in mothers prescribed the medication of interest compared to the frequency of occurrence of the outcome of interest in mothers not prescribed the medication of interest for each medication/outcome pair. IC values that are positive indicate that the outcome and prescribed medication occur more frequently together than would be expected due to chance if both events were independent. In brief the observed counts (a,b,c,d from a two-by-two table) are assumed to have a Multinomial distribution (pa,pb,pc,pd,n). With a Dirichlet prior distribution for pa pb pc and pd the corresponding posterior distribution is also a Dirichlet distribution. Assuming an uninformative prior likelihood, 100,000 random samples from the proposed posterior Dirichlet distribution can be generated and the median IC with its 95% credible intervals obtained [27]. Pairs with a positive lower 95% credible interval have sufficient evidence that they are occurring more frequently than would be expected due to chance and are classified as signals.

Our new method of hierarchical modelling will then use these results to identify groups in the data using bi-clustering techniques. For this method, pairs with a positive lower 90% credible interval using the IC are considered ‘potential signals’. A group is defined as containing all medication/outcome pairs where all medications in the group have a potential signal with the same outcomes in the group. Medications with similar pharmacological properties are likely to be in the same groups, but the actual group membership is determined purely by the data. These groups will then be used to calculate an observed to expected ratio, adjusted for groupings, for each medication/outcome pair.

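### The IC model assumes independent units although women can contribute several pregnancies, so intervals are too narrow for pairs where both prescription and outcome recur within women

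*Protocol article*

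**What the plan says.** Study population: "An individual woman can contribute more than one pregnancy". Only non-singleton pregnancies are excluded on grounds of the pregnancy itself; nothing selects one pregnancy per woman.

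Objective 2: for each medication/outcome pair, the counts in the two-by-two table "are assumed to have a Multinomial distribution", with a Dirichlet prior and 100,000 posterior draws. The comparison is described as "comparing the frequency of occurrence of the outcome of interest in mothers prescribed the medication of interest" against mothers not prescribed it. The decision rule is: "Pairs with a positive lower 95% credible interval have sufficient evidence that they are occurring more frequently than would be expected due to chance". A looser rule, a positive lower limit of the 90% interval, decides which pairs enter the bi-clustering. The hierarchical model that follows is described with a group component and a pair-specific component, and with no component for the woman.

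Objective 1: "Rates of prescribing of each medication category will be calculated per 1000 pregnancies", and the factors behind prescribing are modelled "using multivariable logistic regression models including variables such as maternal age, ethnicity, geographical region, deprivation, and comorbidities". The text does not say how variances are estimated.

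The Limitations section mentions multiple testing and correlation among exposures and outcomes, but not repeat pregnancies of the same woman.

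**The concern.** With about 20 years of records, many women will appear more than once. A woman on a long-term medicine in one pregnancy is likely to be on it in the next, and several of the listed outcomes tend to recur. Two such pregnancies carry less information about the association than two pregnancies of different women, yet a multinomial likelihood counts them as two full observations.

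The interval is itself the screening rule, so understated width turns directly into extra signals. The extra signals are not spread evenly: they fall on pairs where both exposure and outcome persist within a woman. This can affect which pairs enter the bi-clustering, hence the groups and the group means in the hierarchical model, and which pairs reach prioritisation, from which only three go on to a cohort study.

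**Working it through.** **Unit of analysis.** The Objective 2 text speaks of mothers, so the unit is not stated outright. The pregnancy is the workable reading: exposure is defined by pregnancy dates and analysed by trimester, and outcomes such as miscarriage, stillbirth, premature delivery and size for gestational age belong to one pregnancy. Counting women would need a rule for collapsing several pregnancies into one record, and the article gives none.

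**Inputs.** The article gives no sample size, no distribution of pregnancies per woman and no correlations, so there is no stated figure to reproduce. Everything below is assumed:
- m, the size-weighted mean number of pregnancies per woman (sum of squared counts divided by sum of counts): 1.3 to 2.3
- rho_x, within-woman correlation of exposure: 0.5 to 0.6 for a long-term medicine
- rho_y, within-woman correlation of outcome: 0.2 to 0.5 for a recurrent condition

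**Formulas**, for an association near the null:
- Design effect DE = 1 + (m − 1) × rho_x × rho_y
- True SE / naive SE = √DE
- False-signal rate at the 95% rule = P(Z > 1.96/√DE), nominal 2.5%
- Rate at the 90% rule = P(Z > 1.645/√DE), nominal 5%

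**Results**

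| m | rho_x | rho_y | DE | √DE | 95% rule | 90% rule |
|---|---|---|---|---|---|---|
| 1.3 | 0.5 | 0.2 | 1 + 0.3×0.10 = 1.03 | 1.015 | P(Z>1.931) = 2.7% | P(Z>1.621) = 5.3% |
| 1.8 | 0.5 | 0.2 | 1 + 0.8×0.10 = 1.08 | 1.039 | P(Z>1.886) = 3.0% | P(Z>1.583) = 5.7% |
| 2.3 | 0.6 | 0.5 | 1 + 1.3×0.30 = 1.39 | 1.179 | P(Z>1.662) = 4.8% | P(Z>1.395) = 8.2% |

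The m = 1.8 row corresponds to 60%, 30% and 10% of women with 1, 2 and 3 pregnancies: (0.6×1 + 0.3×4 + 0.1×9)/(0.6 + 0.6 + 0.3) = 2.7/1.5 = 1.8.

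**Outside that range**
- rho_x = 0 or rho_y = 0: DE = 1, no effect.
- rho_x = 0.3, rho_y = 0.1, m = 1.8: DE = 1.024, false-signal rate 2.6%.
- rho_x = −0.3, m = 1.8, rho_y from 0.1 to 0.5: √DE from 0.99 to 0.94, so the naive interval is slightly too wide.
- Heaviest case tried (40%, 35%, 15% and 10% of women with 1 to 4 pregnancies; rho_x 0.8, rho_y 0.5): DE = 1.574, false-signal rate 5.9%.

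**Simulation of the IC itself** under no association: 60,000 women, the 60/30/10 split, exposure 2%, outcome 5%, prior 0.5 per cell, 400 replicates of 2,000 draws.

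| rho_x / rho_y | SD of IC / naive posterior SD | False signals, 95% rule |
|---|---|---|
| 0 / 0.3 | 1.02 | 2.0% |
| 0.5 / 0.2 | 1.03 | 2.75% |
| 0.8 / 0.5 | 1.20 | 5.0% |

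The Monte Carlo SE of the rates is 0.7 to 1.1 percentage points. For the last two rows the formula gives ratios of 1.04 and 1.15 and rates of 3.0% and 4.4%, which agrees within that error.

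**Objective 1.** For a covariate fixed within a woman, such as ethnicity, rho_x = 1. With m = 1.8 and rho_y from 0.1 to 0.7, √DE runs from √1.08 = 1.04 to √1.56 = 1.25. An unclustered logistic standard error would be too small by that factor.

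**The case against.** Four points can be made against this.

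1. A reader might infer that every credible and confidence interval in the study is too narrow. The documents do not support that. The inflation depends on the product rho_x × rho_y. It is nil for sporadic short courses or for outcomes that cannot recur, such as maternal death, and it reverses if exposure is negatively correlated within women. This stands.

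2. A reader might also infer that the logistic models are specified to treat pregnancies as independent. The Objective 1 text does not say so. It is silent on variance estimation, and clustered standard errors, GEE or a random intercept may well be in an analysis plan that is not shown. This stands too. The Objective 1 part is a request for a statement, not an error found. Prescribing in under-represented groups also enters prioritisation without any stated interval or significance rule.

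3. The IC description is expressly brief and speaks of mothers. The pregnancy as unit is therefore an inference, though a strong one. If mothers are meant literally, a collapsing rule is needed, so the text has to be reconciled with the Study population section either way.

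4. The screen is hypothesis-generating and deliberately unadjusted for confounders. Signals then pass through evidence review, co-medication checks and workshops, and the effect on any one pair is modest. These steps limit the consequence. They do not correct the interval, and the interval decides which pairs reach them.

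**Conclusion.** The point holds for Objective 2 in limited form. The article fixes a likelihood that needs independent units, allows several pregnancies per woman, and describes nothing that reconciles the two. For pairs where prescription and outcome both recur within women, IC intervals should be about 1.5% to 18% wider, and the false-signal rate per pair is about 2.7% to 4.8% instead of 2.5% (5.3% to 8.2% instead of 5% at the bi-clustering threshold). These figures rest on assumed correlations and pregnancies per woman, on the pregnancy being the unit counted, and on a normal approximation near the null. Other pairs are little affected or not at all. The consequence is a moderate excess of signals concentrated on chronic medicines with recurrent conditions, which is worth correcting before the signal detection is run. It does not invalidate the approach.

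**What to change.** 1. In Objective 2, state that the pregnancy is the unit of analysis and that repeat pregnancies of the same woman are allowed for.
2. Obtain the IC limits by resampling women, for example a Bayesian bootstrap with one random weight per woman applied to all her pregnancies. It is enough to do this for pairs that cross the 90% or 95% limit under the Dirichlet model, and before the bi-clustering, so that the groups are built on the corrected limits.
3. Alternatively, rerun those pairs with one randomly chosen pregnancy per woman. This discards data: under the 60/30/10 split it keeps 1/1.5 = 67% of pregnancies. If exposed cases fall in proportion, intervals widen by about √1.5 = 1.22 from that alone, so a pair that drops out is not thereby shown to be spurious.
4. In Objective 1, state that logistic standard errors are clustered on woman.

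Dividing the counts by a design effect is not recommended, because it needs correlations specific to each pair that nobody has supplied.

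Cost: wording, computing time for the flagged pairs in each exposure window, slightly wider intervals and slightly fewer signals. Woman-level resampling is unstable when exposed cases are very few; for such pairs the Dirichlet limits should be shown alongside.
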